**Methods/Design:**

A total of 340 individuals with type 2 diabetes will be randomised, either to the routine care arm, or to the intervention arm in which participants receive the Telephone-Linked Care (TLC) Diabetes program in addition to their routine care. The intervention requires the participants to telephone the TLC Diabetes phone system weekly for 6 months. They receive the study handbook and a glucose meter linked to a data uploading device. The TLC system consists of a computer with software designed to provide monitoring, tailored feedback and education on key aspects of diabetes self-management, based on answers voiced or entered during the current or previous conversations. Data collection is conducted at baseline (Time 1), 6-month follow-up (Time 2), and 12-month follow-up (Time 3). The primary outcomes are glycaemic control (HbA1c) and quality of life (Short Form-36 Health Survey version 2). Secondary outcomes include anthropometric measures, blood pressure, blood lipid profile, psychosocial measures as well as measures of diet, physical activity, blood glucose monitoring, foot care and medication taking. Information on utilisation of healthcare services including hospital admissions, medication use and costs is collected. An economic evaluation is also planned.

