#### Intervention arm

Intervention participants also continue their routine medical care. In addition, they receive the TLC Diabetes program which was developed collaboratively between the Australian research team and USA researchers at the Medical Information Systems Unit, Boston University [20,21]. The TLC Coordinator, whose role is to support intervention group participants in all aspects of use of the TLC Diabetes program, meets with participants within one week of their Time 1 data collection to provide them with the TLC Diabetes kit containing the TLC Handbook, an *ACCU-CHEK*^® ^*Advantage *glucose meter, test strips, and a Bluetooth™ device with which to upload their blood glucose results to the TLC Diabetes system. The TLC Handbook contains instructions and general information on the TLC Diabetes program, a number of Diabetes Australia diabetes management fact sheets plus sheets on which to record notes and information related to the program. A quit smoking information pack, containing a self-help booklet and brochures, is also provided to current smokers. During this meeting, participants also receive instructions on how to operate the glucose meter and the uploading Bluetooth™ device and complete a training call to the TLC Diabetes system. Participants are asked to perform all blood glucose self-monitoring with the study glucose meter and to upload its readings immediately preceding their weekly telephone conversations with the TLC system.

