### Study integrity

The study design is according to the recommendations of the CONSORT statement for randomised trials of non-pharmacologic treatment [22]. Randomisation to an experimental group occurs after the Time 1 baseline assessment is completed. Arm allocation is conducted using a 4 × 4 block randomised block design with the participant as the unit of randomisation. Due to the complex nature of the intervention, it is not possible to blind research staff to group allocation. The intervention protocol is documented and the data generated during the calls made by participants is stored in the TLC database. All analyses will be conducted based on the principle of intention to treat.

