**Secondary outcome variables**	
Blood lipids	Total cholesterol, LDL cholesterol, HDL cholesterol, triglycerides
Insulin sensitivity	HOMA score
Kidney function	Creatinine and estimated Glomerular Filtration Rate (e-GFR)
Blood pressure	Measured twice using Welch-Allyn electronic sphygmomanometer on same arm. A third measure is taken when the first two readings differ by more than 10 mmHg and 6mmHg for systolic and diastolic blood pressure respectively.
Body Mass Index (BMI)	Calculated from height and weight measured by research staff
Waist and hip circumference	Measured by research staff according to WHO MONICA project guidelines [23]
Diet	Anti Cancer Council of Victoria Food Frequency Questionnaire [30] (ACCVFFQ)
Physical activity	Active Australia Survey [29]
Self-efficacy (nutrition and physical activity)	Self-efficacy scales [28]
Anxiety and depression	Hospital Anxiety and Depression Scale [26]
Social support	ENRICHD Social Support Inventory [27]
Smoking	Self-report
Adherence to recommendations for blood glucose testing, foot-care and medication	Summary of Diabetes Self-Care Activities [31]
Health care service utilisation, except hospital admissions	Self-report for visit to health professionals, usage of hospital services not involving admissions and medications
Hospital admissions	Electronic records maintained by Queensland Health, plus self-report for admissions to private hospitals
Co-morbidities	Self-report

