#### Intervention implementation

Adherence to the program is assessed by the proportion of completed calls to the system relative to the expected number of calls, time interval between calls, and call duration. In addition, satisfaction with and perception of usefulness of the intervention are assessed by self-administered questionnaire at Time 2 and a semi-structured interview at Time 3.

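### The stated reason for not blinding research staff does not cover whoever takes the Time 2 and Time 3 body measurements, leaving waist, hip and weight open to avoidable detection bias

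*Protocol article*

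**What the plan says.** All statements are in the protocol article.

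- **Blinding (Study integrity):** "Due to the complex nature of the intervention, it is not possible to blind research staff to group allocation". No exception is made for those who assess outcomes.
- **Timing (Study integrity):** "Randomisation to an experimental group occurs after the Time 1 baseline assessment is completed".
- **Delivery (Abstract, Methods/Design):** "The TLC system consists of a computer with software designed to provide monitoring, tailored feedback and education on key aspects of diabetes self-management".
- **Support (Intervention arm):** "The TLC Coordinator, whose role is to support intervention group participants in all aspects of use of the TLC Diabetes program". This section and the text that follows it give the Coordinator the kit, the training call, the clinical targets, the support calls and the follow-up of email alerts.
- **Body measurements (Table 1, secondary outcomes):** BMI is "Calculated from height and weight measured by research staff"; waist and hip are "Measured by research staff according to WHO MONICA project guidelines".
- **Blood pressure (Table 1):** "Measured twice using Welch-Allyn electronic sphygmomanometer on same arm", with a fixed rule for a third reading. No operator is named.
- **Questions about the programme (Intervention implementation):** "satisfaction with and perception of usefulness of the intervention are assessed by self-administered questionnaire at Time 2 and a semi-structured interview at Time 3". Their order relative to the physical measurements is not given.

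**The concern.** The protocol treats the lack of blinding as a necessary consequence of the intervention. That holds for those who receive the programme and for the person who supports them. Someone who takes a waist measurement at 6 or 12 months delivers nothing and needs neither the allocation nor the call data.

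Tape circumferences depend partly on the observer, through tape position and tension. If measurers know the arm and expect a benefit, a small difference in waist or hip cannot be separated from a difference in how the tape was read. Weight and height leave less room for this but are taken by the same unblinded group. The risk is avoidable, and a larger sample or a different analysis would not remove it.

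**Working it through.** **Step 1. Does the reason reach the measurer?**

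| Role | What the article has them do | Does complexity prevent blinding? |
|---|---|---|
| Participant | Weekly calls, glucose meter and uploading device | Yes |
| TLC Coordinator | Kit, training, clinical targets, support calls, alerts | Yes |
| Automated system | Delivers the conversations | Not applicable |
| Research staff measuring height, weight, waist and hip | Physical measurements at the hospital visit | No reason given that applies to them |

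The blinding sentence merges the last row with the others. The article describes no masked assessor.

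**Step 2. Which measurements are exposed?**

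- Baseline is not exposed, because it is completed before randomisation. Only Times 2 and 3 are.
- Waist, hip, height and weight are exposed, because research staff are named as the measurers.
- HbA1c is a blood test (Sample recruitment procedures has a hospital phlebotomist take the baseline specimen), so the measurer has no influence on it.
- The behaviour, psychosocial and health care utilisation questionnaires are self-administered (Measurement). SF-36v2 presumably is too, although it is not named there.
- Blood pressure is little exposed, given the electronic device and the fixed third-reading rule.

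**Step 3. What size could it have?** The article gives no figure to reproduce for this point, so this is an illustration.

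Inputs:
- Completers: 340 × 0.70 = 238 (Sample size calculations), taken as 119 per arm.
- SD of waist change: 5 cm, an assumption.
- Differential reading between arms, with no true effect: 0.5 to 1.0 cm, an assumption.

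Standard error of the difference in mean change:

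SE = SD × √(2/n) = 5 × √(2/119) = 0.648 cm

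Shift in SE units: δ = bias / SE
- 0.5 / 0.648 = 0.77
- 1.0 / 0.648 = 1.54

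Two-sided rejection probability at 5%: Φ(−1.96 + δ) + Φ(−1.96 − δ)
- δ = 0.77: 0.117 + 0.003 = 0.12
- δ = 1.54: 0.338 + 0.000 = 0.34

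Only the ratio of bias to SD matters: 0.5/5 = 0.1 gives 12% and 1.0/5 = 0.2 gives 34%. If the SD were 10 cm, a 1.0 cm bias would have ratio 0.1 and give 12%. If it were 2.5 cm, a 0.5 cm bias would have ratio 0.2 and give 34%.

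**The case against.** The case on the other side is substantial.

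- **The outcomes are secondary.** The hypotheses and aims concern HbA1c, SF-36v2 and cost-effectiveness, and the QALYs derive from SF-36v2. This stands. A reader might infer that the primary results are compromised, but the documents do not support that. SF-36v2 remains open to reporting bias because participants know their arm, which blinding the measurer would not cure.
- **Blood pressure.** A reader might infer that it too is taken by staff who know the arm. Table 1 names no operator for it, and the device and third-reading rule limit observer influence. It should not be counted with the tape measurements.
- **Other safeguards exist.** Baseline precedes randomisation, waist and hip follow the WHO MONICA guideline, and each participant is assessed at the same location throughout. These limit discretion but do not mask anyone, so the objection stands in part.
- **The size is assumed.** This stands. The arithmetic shows what would follow if a bias existed; it is no evidence that one of this size is likely.
- **Staffing is unknown.** No staff numbers are given, and the article does not say whether the Coordinator also takes measurements. It cannot be claimed that blinding needs no extra person at either hospital, nor that the Coordinator is the measurer.
- **The route of unmasking is uncertain.** The Time 2 satisfaction questionnaire is self-administered and the order of the visit is not stated. These questions could reveal the arm, but the article does not show that they do.

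None of this supplies a reason why a separate measurer could not be kept unaware of the arm.

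**Conclusion.** The point holds in a limited form. The justification given for not blinding research staff applies to participants and the Coordinator, but not to those who take the Time 2 and Time 3 body measurements. Waist and hip, and to a lesser degree weight and BMI, are therefore open to detection bias that could be reduced.

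The 12% to 34% false-positive rate for waist is illustrative. It rests on an assumed SD of change of 5 cm, an assumed differential reading of 0.5 to 1.0 cm, equal arms of 119 and a simple comparison of mean changes rather than the planned analysis of covariance. Severity is minor to moderate: no primary outcome is affected, but the stated reason is wrong for these measurements and the remedy is modest.

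**What to change.** Replace the blinding sentence under Study integrity with:

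> Participants and the TLC Coordinator cannot be blinded. Time 2 and Time 3 anthropometric measurements are taken by existing research staff other than the TLC Coordinator, without access to the allocation list or the TLC database. Participants are asked not to disclose their arm. The satisfaction questionnaire and the interview follow all measurements, and the interview is done by someone other than the measurer and the TLC Coordinator. Any unmasking is recorded.

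The interviewer should not be the Coordinator because participants may be reluctant to criticise the programme to the person who supported them.

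Where existing staffing at a site does not allow this, give staffing as the reason in place of the intervention's complexity, and interpret the anthropometric results as unblinded. Even there, placing the intervention-specific questions last and keeping the Coordinator from measuring, where possible, would reduce the bias.

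The cost is constraint on rostering and on the order of the visit. No new procedure, endpoint or sample size is needed. Some participants will still reveal their arm, and the record of unmasking will show how often.

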### Measurement

All assessments (Table 1) are administered at the PAH or RBWH but at the same location for Time 1, 2 and 3. Blood specimens are collected according to Queensland Health guidelines. Waist and hip circumferences are measured according to WHO MONICA guidelines [23]. Behaviour, psychosocial and health care utilisation (HCU) questionnaires are self-administered.

**Table 1 T1:** Primary and secondary outcome measures for times 1, 2 and 3

Variable	Instrument
**Primary outcome variables**	
Glycaemic control	HbA1c
Quality of life	SF-36v2 [24,25]

**Secondary outcome variables**	
Blood lipids	Total cholesterol, LDL cholesterol, HDL cholesterol, triglycerides
Insulin sensitivity	HOMA score
Kidney function	Creatinine and estimated Glomerular Filtration Rate (e-GFR)
Blood pressure	Measured twice using Welch-Allyn electronic sphygmomanometer on same arm. A third measure is taken when the first two readings differ by more than 10 mmHg and 6mmHg for systolic and diastolic blood pressure respectively.
Body Mass Index (BMI)	Calculated from height and weight measured by research staff
Waist and hip circumference	Measured by research staff according to WHO MONICA project guidelines [23]
Diet	Anti Cancer Council of Victoria Food Frequency Questionnaire [30] (ACCVFFQ)
Physical activity	Active Australia Survey [29]
Self-efficacy (nutrition and physical activity)	Self-efficacy scales [28]
Anxiety and depression	Hospital Anxiety and Depression Scale [26]
Social support	ENRICHD Social Support Inventory [27]
Smoking	Self-report
Adherence to recommendations for blood glucose testing, foot-care and medication	Summary of Diabetes Self-Care Activities [31]
Health care service utilisation, except hospital admissions	Self-report for visit to health professionals, usage of hospital services not involving admissions and medications
Hospital admissions	Electronic records maintained by Queensland Health, plus self-report for admissions to private hospitals
Co-morbidities	Self-report

#### Primary and secondary outcome variables

Primary outcome variables are: HbA1c and health-related QoL measured by the SF-36v2 [24,25]. Secondary outcome variables include: clinical measures (blood lipid profile, body mass index [BMI], waist and hip circumferences, blood pressure), psychosocial outcomes (depression and anxiety symptoms [26], social support [27]), nutrition and physical activity self-efficacy [28], physical activity [29], diet [30], adherence to foot-care, medication taking and blood glucose testing [31]. Information pertaining to HCU (visits to health practitioners, hospital admissions, other hospital services and medications), healthcare costs and costs of the intervention is also collected. The measures for these variables are summarised in Table 1.

#### Intervention implementation

Adherence to the program is assessed by the proportion of completed calls to the system relative to the expected number of calls, time interval between calls, and call duration. In addition, satisfaction with and perception of usefulness of the intervention are assessed by self-administered questionnaire at Time 2 and a semi-structured interview at Time 3.

#### Socio-demographic variables

Self-reported socio-demographic variables include gender, age, ethnicity, marital status, education, employment status, private health insurance status and household income.

### Data analyses

Assessment of similarity of baseline characteristics across randomised groups will be performed using appropriate summary statistics. If any imbalances of characteristics between the two groups are identified, these will be adjusted for in the main analytical modelling as supplementary analyses. Evaluation of the TLC Diabetes intervention effect will be based on an intention-to-treat analysis. Analysis of covariance (with baseline score as the covariate) will be fitted to estimate differences by intervention group in changes over time at each time point. Analysis across all time points using all available data, including as much as possible those of participants lost to follow-up, will employ generalised estimating equations. Results will be expressed as estimated mean changes in primary and other outcome variables by group, and as overall mean excess intervention over routine care effects, all with corresponding 95% confidence intervals.

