#### Sample size calculations

A total of 340 eligible participants will be recruited to the study. It is anticipated that there will be an attrition rate of up to 30% over the 12 months of follow-up, so we expect complete data on 238 participants. With 238 completing participants, we shall be able to detect, with 90% power and type I error of 5% (two-tailed), excess intervention effects over routine care effects of at least 0.4% (from baseline 8.9% to 8.5%) in HbA1c. The calculations for HbA1c were based on standard deviations of change of 1% in both groups, conservatively estimated assuming maximum physiological range of 3% improvement or deterioration of individuals. An effect size of 0.4% in our primary outcome, HbA1c, was chosen for our sample size calculations as per Toobert [18], who calculated that a change of 0.4% translates into a clinically meaningful 14% reduction in risk of diabetes complications based on the analysis of the UK Prospective Diabetes Study in patients with type 2 diabetes. For SF-36v2 physical and mental component summary scores, a sample of 238 completed participants has 90% power to detect a difference of 3.9 units (assuming standard deviation of 10 [19]).

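### The 12-month ANCOVA appears to discard Time 2 data of later dropouts, and is biased if post-Time 2 dropout depends on response differently by arm

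*Protocol article*

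**What the plan says.** The protocol article, Data analyses, names two methods. The first works visit by visit, separately for Time 2 and Time 3: "Analysis of covariance (with baseline score as the covariate) will be fitted to estimate differences by intervention group in changes over time". The second is longitudinal: analysis "across all time points using all available data, including as much as possible those of participants lost to follow-up, will employ generalised estimating equations". Only the second is credited with bringing in people who leave.

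Study aims makes both Time 2 (6 months, after the intervention) and Time 3 (12 months) part of the primary aim. Sample size calculations allows for an "attrition rate of up to 30% over the 12 months of follow-up" and continues "so we expect complete data on 238 participants". Study integrity says "All analyses will be conducted based on the principle of intention to treat".

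**The concern.** A Time 3 ANCOVA with baseline as the only earlier measurement can use a participant only if Time 3 was observed. Someone who attended Time 2, had a poor HbA1c result and then left contributes nothing to the 12-month estimate, although the Time 2 value predicts the missing one. If that selection works differently in the two arms, those who remain are no longer comparable given baseline, and the 12-month contrast moves.

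Arm-specific selection is plausible here but not documented. Only the intervention arm receives weekly calls, meter uploads and tailored feedback, and research staff are not blinded. If poor responders leave mainly from the intervention arm, the error favours the intervention.

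**Working it through.** **Inputs from the article.** 340 randomised, up to 30% attrition, target effect 0.4 HbA1c points, SD of change 1 in each group. The plan's own completer figure reproduces: 340 × (1 − 0.30) = 238.

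**Assumptions not in the article.** 1:1 allocation; SD 1 at every visit; correlation 0.5 between visits. These give the stated SD of change: √(1 + 1 − 2 × 0.5) = 1. Further: Time 2 complete, 30% missing at Time 3 in each arm, and log-odds of dropout rising by 1 per SD of the driving variable.

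**Large-sample simulation of the Time 3 effect (truth −0.40)**

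| Dropout depends on | ANCOVA, observed cases | GEE, independence | GEE, correct exchangeable |
|---|---|---|---|
| nothing (completely at random) | −0.40 | −0.40 | −0.40 |
| baseline, intervention arm only | −0.40 | −0.53 | −0.40 |
| Time 2 HbA1c, both arms alike | −0.40 | −0.40 | −0.40 |
| Time 2 HbA1c, intervention arm only | −0.46 | −0.53 | −0.40 |
| unseen Time 3 HbA1c, intervention arm only | −0.60 | −0.66 | −0.57 |

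With a true effect of zero, the fourth row becomes −0.06, −0.13 and 0.00.

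**Why the ANCOVA moves in the fourth row.** Write r12, r13 and r23 for the correlations between Times 1, 2 and 3, and s for the shift in mean Time 2 HbA1c among those retained in the intervention arm. With SD 1:

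- Independence GEE: bias = r23 × s. The simulated bias is −0.527 − (−0.400) = −0.127, so s = −0.127 / 0.5 = −0.254.
- ANCOVA: baseline removes only the part of the selection that it carries, so bias ≈ (r23 − r12 × r13) × s = (0.5 − 0.25) × (−0.254) = −0.064. This agrees with the simulated −0.46.

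If both arms have the same s, the two shifts cancel. That is the third row.

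**Range over the assumed correlations, same s.**

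- All correlations 0.65: (0.65 − 0.4225) × 0.254 = 0.058.
- Baseline correlations 0.5 and r23 = 0.65: (0.65 − 0.25) × 0.254 = 0.10.

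**Trial-sized simulations** (170 per arm, 26 to 31% missing at Time 3, Time 2 to Time 3 correlation 0.65, 2,000 trials per scenario, dropout on Time 2 in the intervention arm only):

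- True effect −0.4: ANCOVA bias −0.067, likelihood model +0.003.
- True effect 0: ANCOVA bias −0.089, likelihood model +0.006.

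A further set with correlations of 0.5 to 0.65 gave ANCOVA bias of about −0.065 to −0.07 and about 0 for the likelihood model. Standard errors of the two methods were within 0.002 of each other (0.097 to 0.114 against 0.099 to 0.115).

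**Dropout on Time 2 in both arms.** ANCOVA bias was 0.00 in the table and about 0.01 in the further set. The largest value in any run was 0.026, towards the null.

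**Size against the target.** 0.06 / 0.4 = 15%; 0.07 / 0.4 = 17.5%.

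**The case against.** Several stronger readings are tempting, and the documents do not support them.

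- **A reader might infer that both methods need dropout completely at random.** This is wrong for the ANCOVA. It conditions on baseline and arm and, with a correct mean model, is valid when dropout depends only on those (second row of the table). At Time 2, baseline is the only earlier value of the outcome, so the concern is confined to Time 3. For GEE, complete randomness (or dropout driven only by modelled covariates) is what guarantees validity under any working correlation. With a well-specified correlation and near-normal outcomes, GEE is approximately valid under missing at random, and in these simulations exchangeable GEE did as well as the likelihood model.
- **A reader might infer that poor responders leaving is enough to bias the result.** It is not. The relation between dropout and response has to differ by arm.
- **A reader might blame the weekly call burden.** The calls run for 24 weeks and end at about Time 2, whereas the bias shown arises from leaving after Time 2. Call burden would mainly cause earlier losses, which the proposed model does not recover either.
- **A reader might count the unstated working correlation, weighting, imputation or missing-data sensitivity analysis as defects.** A condensed article commonly leaves these to a full protocol or SAP, and neither is shown.

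It is also fair to say that the article never calls the ANCOVA an observed-case analysis. That is an inference, drawn from the absence of any imputation and from the contrast with the GEE sentence. The article also gives the two methods different roles. What survives is narrower: the stated visit-by-visit ANCOVA, read as it appears to be meant, leaves out available Time 2 information from the 12-month contrast.

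**Conclusion.** The point holds in this limited form. With up to 30% attrition expected, the Time 3 ANCOVA is exposed to an avoidable bias if dropout after Time 2 depends on Time 2 response differently by arm.

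Under one-arm dropout the bias is about 0.06 to 0.07 HbA1c points in favour of the intervention, 15 to 18% of the target. Less favourable assumptions take it to about 0.09 or 0.10. With dropout alike in both arms it is about 0.01 or less; the one larger both-arms result went towards the null.

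These sizes are illustrative, because the article gives neither between-visit correlations nor a dropout mechanism. They also place all 30% of losses after Time 2. Earlier losses would shrink the part that Time 2 data can correct. The finding does not show that the trial's result will be biased, or that the GEE is invalid.

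**What to change.** For HbA1c and the SF-36v2 physical and mental summary scores, name one primary analysis: a likelihood-based repeated-measures model with Times 2 and 3 as outcomes, unstructured covariance, arm-by-time and baseline-by-time terms, and all participants with any follow-up, analysed in the arm to which they were randomised. Read both the Time 2 and the Time 3 contrasts from it. Keep the observed-case ANCOVA as a sensitivity analysis. State that the primary model assumes data missing at random given arm, baseline and observed follow-up. If a SAP already does this, nothing changes.

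The cost is a change of wording and slightly more analysis work. No new data are needed, and the simulations showed no material loss of precision. Two limits should be stated alongside it: the model does not recover participants lost before Time 2, and it does not correct dropout that depends on unseen values. In the last row of the table every method shown is biased, and a likelihood model would not cure that.
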